#### Biological assessments for the intervention group

Biological assessments will include urinalysis, semen analysis, routine biochemistry, non-routine hormone tests, markers of glucose, lipid and bone metabolism and immunological gene expression profile.

Urine will be screened for AAS and psychoactive substances at inclusion, during intervention and at follow-up. Additionally, routine blood analyses will be conducted at the time of inclusion and every 4 weeks. These regular assessments serve both safety purposes and to monitor physiological markers associated with AAS induced side effects. Throughout the intervention period and at the 6-month and 12-month follow-ups after discontinuation of AAS usage, a comprehensive set of analyses will be carried out. These include evaluation of sex hormone levels, metabolic and hematological status, glucose, insulin production and resistance, liver and kidney function, electrolytes, and immune markers.

Blood and adipose tissue are sampled in fasting condition between 8:00 and 10:00. Blood samples, including serum, EDTA and citrated plasma and RNA (Paxgene tubes) for gene expression profiling at baseline and after 6 and 12 months are prepared and stored in a biobank at −80 °C. Adipose tissue samples are taken from the gluteal region at baseline and after 12 months, immediately snapfrozen and stored in a biobank at −80 °C until gene expression profiling.

##### Physical examination

The physical examination will encompass various assessments to evaluate change in the participants’ health status from current use, during and after the intervention and includes blood pressure (BP), heart rate (HR), Electrocardiogram (ECG), weight, height, body mass index (BMI), auscultation of heart and lungs, evaluation of striae, acne, and gynecomastia. As cardiac hypertrophy is often not detected on ECG screenings among people who use AAS [25], the participants will be referred to routine echocardiography at their local hospital.

**Semen samples** will be analyzed prior to intervention and 6 and 12 months after the intervention start to evaluate change in measures of testicular function and fertility (sperm count, morphology, motility; and vitality) during and after AAS use.

**Testicular volume** will be measured by orchidometer and ultrasound at baseline and follow up at 12 months as increased volume flowing upon cessation of long term AAS use is seen as sign of improved testicular function [26].

**The vascular morphology and -function** will be evaluated by the thickness of intima media of the common carotid artery and by the carotid artery reactivity (CAR). In addition, endothelial function and pulse wave velocity will be measured at inclusion and at follow-up with established methodology at the Section of Vascular Investigation, OUH [12].

**Body composition and fat distribution, including visceral and subcutaneous adipose tissue**, will be assessed by dual energy X-ray absorptiometry (DXA-scan) to evaluate whether there is a difference in body composition (Total lean mass (kg) (TLM), Total fat mass (kg) (TFM), Body fat %, Visceral and subcutaneous adipose tissue (VAT) (g), Android fat (g), fat distribution and bone mineral (BMD) g/cm2 with T-score and Z-score in the following sites: Lumbar spine (LS) (L1-L4), Total hip, Proximal radius, Ultradistal radius, Total body during AAS use and 12 months after AAS-cessation.

##### Biomarker analyses

From the established biobank circulating inflammatory biomarkers including selected cytokines, chemokines and adhesion molecules will be analyzed. Molecular factors in focus are interleukins, tumor necrosis factor, interferon-γ, fibroblast and endothelial growth factors, vascular cell adhesion molecule 1, monocyte chemotactic factor 1 and Brain Derived Neurotrophic Factor.

Analyses of adipose tissue will encompass a comprehensive assessment, of biochemical factors relevant to cardiovascular and other health risks, including immune markers and individual markers’ genetic expression. RNA will be isolated from both the fat tissue and blood samples for further investigation of the regulation (mRNA) of proteins of interest during AAS use and 12 months after cessation of AAS. Notably, alteration in the extracellular matrix within adipose tissue has been linked to glucometabolic disturbances, such as insulin resistance/sensitivity, diabetes, and obesity, which are all relevant health concerns related to AAS use.

#### Registration of adverse events

As a safety measure, an eye examination will be conducted at an optometrist at inclusion and after the intervention. The Common Terminology Criteria for Adverse Events (CTCAE) version 5 is used to classify adverse events at follow-up examinations every 4th week during the intervention. The participants can contact the research physicians ([name] and [name]) by phone or mail during the intervention period for any experienced side effect(s). Any event requiring medical intervention is registered (CTCAE level 2 or above). Medication-related Severe Adverse Events (SAEs) and Suspected Unexpected Severe Adverse Reactions (SUSARS) are reported to the Norwegian Medicines Agency within 7 days for fatal/life threatening events/cases and for other SUSARs, within 15 days.

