## Description of protocol

### Aims

The primary aim of the present study is to explore whether the 16 weeks therapy model with clomiphene citrate (CC) leads to stimulation of endogenous luteinizing hormone (LH) and testosterone production, if the treatment model is safe, and if the model is more effective in reducing AAS withdrawal symptoms compared to no intervention. The secondary aims are to detect health risks during ongoing AAS use in the intervention group only and assess whether and to what extent the health risks are reduced 12 months after cessation of AAS.

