### The intervention

Rahnema and colleagues presented a treatment model to prevent severe symptoms of hypogonadism during cessation of AAS including use of CC, a Selective Estrogen Receptor Modulator (SERM), to restart the HPG-axis [14]. CC selectively binds to estrogen receptors and acts as a receptor antagonist with week estrogen activity in the hypothalamus which leads to blocked negative feedback inhibition. This leads to increased gonadotropin-releasing hormone (GnRH) pulsation in the hypothalamus, increased release of luteinizing hormone (LH) from the pituitary gland and finally increased levels of endogenous testicular testosterone. CC is approved for short-term treatment of female infertility. CC as off-label treatment has been found safe, tolerable and effective to improve serum levels of testosterone, symptoms of hypogonadism and infertility in men with hypogonadism of other causes than AAS use [22,23]. In the reviewed studies, dosages of 25 mg daily for up to 12 months, 50 mg daily for up to 6 months, and 25–50 mg every second day for 1, 2 and 3 years or more were administered. The majority of these investigations reported no occurrence of major side effects. Side effects reported were: headache, dizziness, mood changes, blurred vision/visual change, breast tenderness/gynecomastia, secondary polycythemia without need for phlebotomy and a few cases of elevated liver enzymes [22,23].

This protocol involves a slightly modified version of the 16 week therapy model outlined by Rahnema and colleagues involves administration of 25 mg CC orally every second day for 16 weeks [11]. Testosterone 50 mg is given transdermal daily for the first 4 weeks as rescue medication before the expected endogenous Testosterone (T) response, see Fig. 2. The target T level during the intervention is set at 20 nmol/l. If the endogenous LH and T response is poor (T < 10 nmol/l) after 4 weeks, human chorionic gonadotropin (hCG) will be added as 1500 IE subcutaneous injection twice a week, as rescue medication. If the endogenous T response is still poor after 8 weeks, the same dose will be given three times a week for four more weeks or throughout the intervention. If poor response on endogenous LH and T levels below lower limit of normal range after 16 weeks intervention *and* the participant experiences severe symptoms of hypogonadism; testosterone replacement therapy (TRT) and referral to endocrinologist will be considered.

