### Outcomes and instruments

Primary outcomes:(1)*Changes in self-reported symptoms of hypogonadism,* mental health state, and symptoms associated with AAS use. The following will be assessed for both the intervention and comparison group: fatigue, depression, suicidal ideation, anxiety, wellbeing, sexual dysfunction, sleep quality, aggression, and body dysmorphia.(2)*Side effects related to CC* will be specifically evaluated for the intervention group.

Secondary outcomes:

Change in measures of physical health from baseline to follow-up for the intervention group:•Weight, body mass index (BMI), degree of striae, acne, androgen alopecia and gynecomastia•Endocrine status, metabolic status, liver and kidney function (blood tests)•Cardiovascular status: Blood pressure, electrocardiogram (ECG), vascular morphology (carotid intima-media thickness and pulse wave velocity) and -function (flow-mediated dilation and carotid artery reactivity)•Body composition; total fat mass, visceral and subcutaneous fat tissue, total lean mass, and bone mineral density•Testicular volume and sperm quality•Immunological biomarkers, analyzed from biobanked blood and adipose tissue samples

Change in measures of mental health risks from baseline to follow-up after 12 months:•Depression and anxiety levels, AAS dependence, body image concerns, aggression, AAS use, and adherence to SUD treatment

Study participants included for the intervention will be screened for eligibility at baseline and examined to assess mental health status, comorbidity, AAS history, AAS dependence and SUDs with validated instruments, see flow chart for study events (Table 1).

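### Clomiphene side effects are a primary outcome with no severity limit, but the only stated registration rule starts at CTCAE level 2, so mild effects may go uncounted

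*Protocol article*

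**What the plan says.** All places are in the protocol article.

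- **Aims.** The primary aim includes finding out "if the treatment model is safe".
- **Outcomes and instruments.** Primary outcome (2) is side effects related to clomiphene, which "will be specifically evaluated for the intervention group". No grade or severity limit is attached.
- **Registration of adverse events.** CTCAE version 5 "is used to classify adverse events at follow-up examinations every 4th week during the intervention". Participants may also contact the study physicians about any side effect. The one rule on registration is "Any event requiring medical intervention is registered (CTCAE level 2 or above").
- **The intervention.** Side effects seen in earlier studies of clomiphene in men are given as "headache, dizziness, mood changes, blurred vision/visual change, breast tenderness/gynecomastia, secondary polycythemia without need for phlebotomy and a few cases of elevated liver enzymes". On severity the section says: "The majority of these investigations reported no occurrence of major side effects". It gives no CTCAE grades and no rates.
- **Data analysis plan.** Reported adverse events are to be summarised descriptively.
- **Sample size determination.** The small sample is justified partly because it allows side effects to be explored.

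**The concern.** An outcome without a severity floor is paired with a registration rule that has one. If sites follow the rule, mild events that need no treatment are not registered. The analysis describes reported events, so those mild events have no stated route into the primary safety result. The result would then lean towards fewer side effects than participants had.

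Mild effects matter here because the study is a pilot meant to explore side effects and to inform later trials, for which tolerability is relevant. An event that nobody registered at the time cannot be recovered reliably afterwards.

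**Working it through.** The plan states no figure on this point, so there is nothing to reproduce. The check has two parts.

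**1. Which expected effects depend on adverse event registration?** Each item in The intervention is set against the other scheduled assessments.

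| Expected effect | Other scheduled measure | Where |
|---|---|---|
| Headache | None dedicated (a general pain VAS only) | Self-reported mental health, well-being and AAS withdrawal symptoms |
| Dizziness | None | – |
| Mood changes | HSCL-10, suicidal ideation item, WHO-5 and aggression VAS, every second week | Same section |
| Visual change | Eye examination at inclusion and after the intervention | Registration of adverse events |
| Breast tenderness/gynecomastia | Gynecomastia examined; tenderness has no dedicated measure | Physical examination |
| Polycythemia | Haematology, with routine bloods every 4 weeks | Biological assessments |
| Raised liver enzymes | Liver function, with routine bloods every 4 weeks | Biological assessments |

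Five of the seven items have a measure that does not depend on grade. Headache and dizziness do not, nor does the tenderness half of the breast item. Vision is measured only before and after treatment, so a symptom that appears and resolves in between rests on adverse event registration. The article does not say that any of these other measures feed into primary outcome (2).

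**2. How much could the threshold hide?** Inputs:

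- N = 25 or 30, the recruitment target for the intervention group (Sample size determination).
- p, the share of men with a given side effect at any grade: **assumed**.
- g, the share of those cases below the registration threshold: **assumed**.

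Expected number registered = N × p × (1 − g). Chance that none is registered = (1 − p(1 − g))^N. With all grades registered the chance of none is (1 − p)^N.

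Worked case: N = 25, p = 20%, g = 75%. Expected at any grade: 25 × 0.20 = 5.0. Expected registered: 25 × 0.20 × 0.25 = 1.25. Chance of none registered: 0.95^25 = 27.7%. With all grades registered: 0.80^25 = 0.4%.

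Results for p = 20%:

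| g | N = 25: expected registered | N = 25: chance of none | N = 30: expected registered | N = 30: chance of none |
|---|---|---|---|---|
| 0 (all grades) | 5.0 | 0.4% | 6.0 | 0.1% |
| 25% | 3.75 | 1.7% | 4.5 | 0.8% |
| 50% | 2.5 | 7.2% | 3.0 | 4.2% |
| 75% | 1.25 | 27.7% | 1.5 | 21.5% |
| 90% | 0.5 | 60.3% | 0.6 | 54.5% |

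Other values of p at N = 25: with p = 10% the chance of none runs from 14.2% (g = 25%) to 77.8% (g = 90%), against 7.2% with all grades. With p = 40% it runs from under 0.1% to 36.0%, against under 0.1%.

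The answer depends almost wholly on g, about which the article says nothing. The table shows that the threshold can matter, not how much it will.

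**The case against.** The best defence is that the rule sets a minimum. It says that events needing intervention are registered; it does not say that milder ones are not. The same section classifies adverse events every fourth week with no grade floor and invites reports of any side effect. The content of the flow chart in Table 2 is not visible in the text reviewed and might list a side-effect assessment. A journal article also leaves much recording detail to the full protocol.

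Part of this stands. That milder events go unrecorded is inferred from the sole stated rule, and the section can be read both ways. But classifying an event or hearing of it is not registering it, and a threshold has little purpose if every grade is registered anyway. Nor is this detail left out for brevity: the article chose to state a threshold, and that threshold does not fit the outcome.

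A second defence is that most listed effects are measured elsewhere. This is correct for five of the seven and narrows the point considerably. It does not close it, since no link from those measures to primary outcome (2) is stated.

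A reader might infer more than the article supports:

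- **That most expected side effects would go uncounted.** No grades or rates are given. The absence of major effects in most earlier studies is not the same as needing no intervention; only polycythemia is described in such terms, "secondary polycythemia without need for phlebotomy and a few cases of elevated liver enzymes" being the relevant wording.
- **That mild mood or visual symptoms would be lost.** Mood is self-reported every second week and falls under primary outcome (1). Vision is examined twice, so only symptoms between the examinations are exposed.
- **That clomiphene effects cannot be told from those of gel, hCG or withdrawal, or that so few men cannot show safety.** Both would be the same under all-grade registration, so neither bears on the threshold.

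**Conclusion.** The point holds in a limited form. The outcome has no severity limit and the only stated registration rule has one, so the two sections need to be reconciled. Followed as written, the rule may leave mild headache, dizziness and breast tenderness out of the primary safety outcome, together with visual symptoms confined to the interval between eye examinations. Any resulting bias is towards fewer side effects.

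The size of the undercount cannot be stated. Under the assumed inputs above it ranges from slight to large, and no single value is supported by the article. The conclusion rests on one reading: that an event is counted for primary outcome (2) only if it is registered under the stated rule.

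**What to change.** Change Registration of adverse events so that every adverse event of CTCAE grade 1 or above is registered at the existing four-weekly visits, whether or not it needs intervention. Report the events descriptively by grade. State that the eye, laboratory, physical examination and questionnaire findings feed into primary outcome (2).

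If all-grade registration is not adopted, restate primary outcome (2) as limited to events of grade 2 or above, so that readers know what the count covers.

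The cost is a little more recording at visits that already take place and already use CTCAE. The change concerns recording only.

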### Data analysis plan

Data analyses will follow a full analysis set, with a per protocol plan. Descriptive statistics will be used when appropriate and for reported adverse events. For between-group comparisons and to control for the effect of baseline characteristics, we plan to use General Linear Mixed Models (GLMM) with a within subject repeated measures design at baseline, 6 months and 12 months. In cases where the outcomes do not meet the normality assumption, we will apply a General Alinear Mixed Models (GAMM) approach. The results of statistical analyses will be performed using 95 % CIs, and a two-sided P value of < 0.05 will be used to indicate statistical significance. General linear models may be utilized in cases where GLMM/GAMM is considered inappropriate. Two sample *t*-tests will be used for between-group comparisons of numerical variables, when we see no need to adjust for confounding variables. Numerical data not following normal distribution will be presented as medians (25th-75th percentiles), using non-parametric tests such as the Wilcoxon rank sum tests (Mann-Whitney) to compare differences between groups. Chi^2^-tests and Fischer's exact will be applied for categorical variables. Per protocol analysis will be applied in cases of missing data to detect any discrepancy that might affect the robustness of the results. All statistical calculations and analyses will be conducted using up-to-date versions of the statistical software STATA and SPSS.

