## Methods and analysis

In this open-labeled non-randomized proof-of-concept intervention study, we aim to include 25–30 AAS-dependent men who struggle to cease their AAS use. The subjects in the intervention group will receive 25 mg chlomiphene citrate every second day following AAS cessation for 16 weeks. The comparison group comprise participants in another study of men who ended AAS use temporarily without the intervention and the groups will be compared on self-reported withdrawal symptoms.

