### Study design

The study includes two sub-studies with

A) *Within-subjects repeated measures design* to monitor the intervention group with physical and mental health parameters and blood sampling prior to intervention start and while still using AAS, during 16 weeks of intervention, and at follow-up at 6 and 12 months (Table 2).

**Table 2 tbl0002:** Flow chart of study events during the study period for the intervention group, modified version of SPIRIT.

B) *Single center – single group – case-comparison design*:

Male participants with AAS dependence and continuous AAS use with the intention to cease use permanently comprise the intervention group. The data from the intervention group will be compared with data from an ongoing study of men who intend to cease a cycle of AAS use temporarily without receiving intervention. Participants from both studies will self-report withdrawal symptoms and other subjective health measures during ongoing use and after cessation. The intervention group will self-report withdrawal symptoms every 2 weeks for 16 weeks of intervention, see Fig. 1.

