#### Self-reported mental health, well-being and AAS withdrawal symptoms

To investigate mental health state, wellbeing and AAS-withdrawal symptoms after AAS cessation, the following self-reporting questionnaires will be administered via a web-app every second week for 16 weeks for both groups and at follow-up at 6 and 12 months for the intervention group: Hopkins Symptom Checklist-10 (HSCL-10) to evaluate psychological distress, suicidal ideation item from Montgomery and Åsberg Rating Scale (MADRS), items from Health-related quality of life (HRQOL) to evaluate sexual function, Shortened Fatigue Questionnaire, WHO-5 Wellbeing Index and Jenkins Sleep Scale (JSS), Body Perception Questionnaire; and Visual Analog Scale (VAS) to measure aggression, cognitive function, body image and pain. Treatment satisfaction will be assessed using VAS for the intervention group only.

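### The between-group mixed model is set at baseline, 6 and 12 months, but after baseline the comparison group is measured only up to week 16, so the model and the data share no post-baseline time point.

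*Protocol article*

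**What the plan says.** The Data analysis plan states the purpose of the model: "For between-group comparisons and to control for the effect of baseline characteristics, we plan to use General Linear Mixed Models (GLMM"). The same sentence goes on to fix its measurement times: "with a within subject repeated measures design at baseline, 6 months and 12 months".

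The section on self-reported mental health, well-being and withdrawal symptoms says who answers the questionnaires and when: "every second week for 16 weeks for both groups and at follow-up at 6 and 12 months for the intervention group". Study design agrees for the treated men: "The intervention group will self-report withdrawal symptoms every 2 weeks for 16 weeks of intervention".

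The comparison serves a primary purpose. Aims asks "if the model is more effective in reducing AAS withdrawal symptoms compared to no intervention". Outcomes and instruments makes change in self-reported symptoms the first primary outcome and says of the symptom domains: "The following will be assessed for both the intervention and comparison group". Methods and analysis names what is compared: "the groups will be compared on self-reported withdrawal symptoms".

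The measures that do fit a baseline, 6-month and 12-month schedule are secondary. The physical ones are introduced as "Change in measures of physical health from baseline to follow-up for the intervention group", and Aims restricts the health-risk question to the intervention group.

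**The concern.** A two-group repeated-measures model can say something about treatment only at times when both groups are observed. Here the model's follow-up times are ones at which only the treated men are measured, and the times at which both groups are measured are not in the model.

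The part of the primary aim that compares symptoms with no intervention therefore has no workable repeated-measures analysis. If this stays, the time points, the method and the contrast for that comparison will be chosen once data are in hand. That matters more than usual here, because the study is open-label and non-randomised, uses many symptom scales, and is meant to supply effect sizes for planning later trials (Scientific rationale for study design; Limitations).

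**Working it through.** The check is one of schedule. The plan gives no figure to reproduce on this point.

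**Step 1. Times in the model.** From the Data analysis plan: baseline, 6 months and 12 months. After baseline that is about weeks 26 and 52.

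**Step 2. Times at which each group reports symptoms.** From the section on self-reported measures:

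| Time | Intervention group | Comparison group | In the stated model |
|---|---|---|---|
| Baseline (ongoing use) | yes | yes | yes |
| Weeks 2, 4, 6, 8, 10, 12, 14, 16 | yes | yes | no |
| 6 months | yes | no | yes |
| 12 months | yes | no | yes |

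The baseline row rests on Study design, which has both groups reporting during ongoing use and after cessation.

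**Step 3. Overlap.** Post-baseline model times {26, 52} against comparison-group times {2, 4, 6, 8, 10, 12, 14, 16}: no element in common. The comparison group contributes baseline records only, so the group-by-time terms at 6 and 12 months cannot be estimated.

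**Step 4. What is left out.** Shared post-baseline occasions: 16 / 2 = 8, none of them in the model. With 25–30 comparison men (Sample size determination), the comparison-group records outside the model number 8 × 25 = 200 to 8 × 30 = 240. This is a ceiling: it assumes complete reporting, and some of these records may follow a restart of steroid use. Treatment ends at week 16, which is 112 days or about 3.7 months, before the first modelled follow-up.

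**Step 5. Illustration of what the fortnightly scores could add.** The finding does not depend on this step. Assumptions: d = 0.4 (the effect named in Sample size determination), 26 per group (half of the stated 52), two-sided 0.05, compound symmetry with correlation ρ = 0.5 to 0.7 (not in the documents), a constant effect over weeks 2–16, complete data and no baseline imbalance. Both analyses adjust for the baseline score, so the comparison is like for like.

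- One time point: residual variance 1 − ρ² = 0.75 (ρ = 0.5) or 0.51 (ρ = 0.7). Effective d = 0.4/√0.75 = 0.46 or 0.4/√0.51 = 0.56. Power is about 37% or 51%.
- Mean of eight: residual variance (1 + 7ρ)/8 − ρ² = 0.5625 − 0.25 = 0.3125, or 0.7375 − 0.49 = 0.2475. Effective d = 0.4/√0.3125 = 0.72 or 0.4/√0.2475 = 0.80. Power is about 72% or 81%.

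An unadjusted single time point gives about 29%. Setting that against 72–81% would credit the gain from baseline adjustment to the repeated measures, so it is not the right comparison.

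**The case against.** **The sentence may merge two analyses.** Study design describes a within-subject part with follow-up at 6 and 12 months and a separate comparison with the untreated men. The analysis sentence appears to attach the first schedule to the second purpose, and a fuller plan may separate them. This is a plausible account of how the conflict arose. It does not remove it: on that reading the 16-week comparison has no stated repeated-measures model at all. The article is not silent here; it fixes time points that conflict with its own schedule.

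**Other methods are listed.** The Data analysis plan also allows general linear models where the mixed model is judged inappropriate, as well as t-tests and rank-sum tests, none tied to a time point. A general linear model can adjust for baseline and could be fitted to 16-week data. A reader might infer that the primary question cannot be answered at all; the documents do not support that. These routes are fallbacks without time points, however, so the contradiction stands.

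**The comparison group is followed up.** A reader might also infer that it has no follow-up data. It has, fortnightly to week 16; only the 6- and 12-month questionnaires are missing.

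**Simply moving the model to weeks 2–16 is incomplete.** Comparison men stop only temporarily, and Table 1 asks for at least 6 weeks between cycles, so some may restart before week 16. Later weeks could then set treated cessation against resumed use. This stands, and the fix has to deal with it.

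**The power illustration is fragile.** Background says that deficiency symptoms first appear weeks after cessation, and Limitations expects the groups to differ, so a constant effect and balanced baselines are optimistic. This too stands; the figures are illustrative only.

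**Conclusion.** The contradiction is real and lies in the article's own text. The stated between-group model has 0 shared post-baseline time points where the schedule offers 8, cannot estimate its group-by-time effect, and omits all the post-baseline symptom data that both groups provide for the first primary outcome. This rests only on the two schedules as written. The timeline figure was not available, but no text gives the comparison group a 6- or 12-month assessment.

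The scope is limited to the comparison of symptoms with no intervention. The other primary elements, hormone stimulation and safety, do not depend on this model. The sentence should nevertheless be corrected before analysis, because the groups differ by design in dependence, pattern of use and intention to stop, and the adjusted longitudinal model is the one this comparison needs.

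**What to change.** Replace the single sentence with two models.

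1. **Between groups.** A mixed model on baseline and weeks 2–16 in both groups, with group, week, group-by-week and baseline score, and one named contrast (a stated week or a stated average over weeks). State how comparison-group scores recorded after a restart of steroid use are handled, and choose the contrast with that in mind.
2. **Within the intervention group.** A repeated-measures model at baseline, 6 and 12 months for the outcomes followed over that period, with no between-group term.

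Say also at which time points the general linear models and simple tests would be used, and under what condition. The cost is a few sentences. No new visits or questionnaires are needed, though the restart rule requires that the date of any restart in the comparison group be known; the article does not say whether the other study records it.
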